## Abstract

**Background:**

Obesity is a highly prevalent condition with multiple adverse health consequences. Widely available first-line treatments for obesity, such as dietary and other lifestyle interventions, typically have only short-term effects. Thus, new treatment approaches are needed. Novel interventions such as Attention Bias Modification Training (ABMT) and mindfulness-based interventions focus on modifying different maladaptive cognitive patterns typically present in people with obesity (e.g. attention bias to food cues); however, their mechanisms of action remain largely unknown. We describe the theoretical basis and the rationale for a study protocol of a feasibility randomised controlled trial (RCT) comparing two attention trainings (ABMT vs Mindfulness Training [MT]) in people with overweight or obesity. The aim of this study is to inform the development of a large-scale RCT in relation to acceptability and attendance rates and to identify preliminary evidence for the interventions’ clinical efficacy and potential underlying mechanisms.

**Design:**

Forty-five adults who are either overweight or obese (minimum body mass index of 25 kg/m^2^) will be randomly allocated to receive eight sessions over eight weeks of either computerised ABMT or MT or be on a waiting list. Clinical and cognitive outcomes will be assessed at baseline, post-treatment (8 weeks) and follow-up (12 weeks post-randomisation). These include mood, body composition and attention biases. Credibility and acceptability of the trainings will be assessed using questionnaires, and recruitment and retention rates will be recorded.

**Discussion:**

Findings will inform the feasibility of developing a large-scale RCT that takes into consideration effect sizes for primary outcome measures and the acceptability of the design. The study will also provide preliminary evidence on the clinical efficacy of two different attention trainings for people with obesity and associated underlying mechanisms.

**Trial registration:**

ISRCTN Registry, ISRCTN15745838. Registered on 22 May 2018.

## Background

Obesity is a highly prevalent condition in the western world, associated with multiple adverse health consequences such as diabetes mellitus, hypertension and some types of cancer [1, 2]. Current treatments for obesity, based on dieting and lifestyle changes, typically have only short-term effects [3–6], presumably because there is little focus on pre-conscious and relatively automatic cognitive processes that may drive overeating in people with obesity [7].

Several studies have investigated the role of reward and of attention control in relation to food in people with obesity and/or binge eating disorder (BED), an eating disorder leading to (and often co-morbid with) obesity. These studies show enhanced reward sensitivity when participants are presented with food cues (both neurally and self-reported) and lower self-regulatory processing [8, 9]. Relatedly, some studies have reported the presence of attention biases to food and other salient cues in obesity and BED [10, 11] presumably due to low attention control for highly rewarding stimuli (e.g. high-caloric food) [12–14].

Attention biases (AB) occur when salient stimuli (e.g. food) capture a person’s attention in comparison to neutral stimuli [15]. Research suggests that people with obesity and/or with BED tend to have AB towards food cues together with a difficulty in disengaging from these cues (as measured with eye-tracking techniques) [11]. Importantly, gaze maintenance on food cues has been shown to contribute to food craving and to subsequent food consumption [10, 16] and AB has been positively associated with body mass index (BMI) [17]. Due to the potential role of AB in eating behaviour, treatment approaches aimed at modifying these biases have been developed [18, 19].

It has been proposed that AB can be targeted directly, using attention bias modification training (ABMT), a form of cognitive bias modification training. Specifically, ABMT has the potential for modifying attention processes towards salient cues [20]. These types of cognitive trainings hold the promise of an accessible treatment option due to their low cost and their potential for self-administration. Moreover, cognitive bias modification trainings, such as ABMT, target specific relatively automatic cognitive processes directly and do not, as in the case of cognitive behavioural therapy (CBT), rely on the patient’s ability to consciously modify maladaptive pre-conscious cognitive processes such as AB.

In the context of overeating, there is a growing body of research on the effects of ABMT. Some studies have focussed on using ABMT experimentally to investigate the potential (causal) role of cognitive processes associated with the onset/maintenance of eating and weight disorders [21]. Others have started to test the clinical impact of ABMT as treatment for overeating tendencies. In these studies, different ABMT paradigms have been used, but the most commonly investigated is the dot-probe task [22].

Even though results have been mixed, some studies using ABMT to modify food-related AB and eating behaviour have shown promising results. One meta-analysis reported a reduction in high-calorie food consumption (medium effect size) after training participants to look away from high-caloric food cues [23]. A second meta-analysis of the effects of different cognitive bias modification trainings (including ABMT) reported a medium effect size in modifying AB towards food cues in individuals with normal weight and with overweight/obesity [24].

In addition, a study using a single session of ABMT to train people with BED to look away from food cues found a significant reduction in subjective food craving after training [25]. Relatedly, a feasibility open trial using eight weekly sessions of ABMT in people with overweight/obesity who binge eat reported encouraging results in reducing weight, eating disorder symptoms, binge eating and AB after training [26]. To date, however, the mechanisms involved in the potential therapeutic effect of ABMT are not clear [27, 28].

Other attention-based treatment approaches, for example, mindfulness-based interventions, have also reported positive results in people with obesity and/or BED. They train participants to attend to the present moment in a non-judgmental manner [29, 30]. This includes identifying internal cues of hunger/satiety and learning to control impulsive or automatic behaviours that could lead to overeating [31]. Systematic reviews and meta-analyses of randomised controlled trials (RCT) of mindfulness-based interventions in people with overweight/obesity have reported post-intervention reductions in binge eating episodes and impulsive eating (large effect sizes) and increases in physical activity (small to medium effects), although the effect of mindfulness on body weight is less clear. In addition, medium effect sizes have been reported regarding improvements on symptoms of depression and anxiety after such interventions [32, 33]. However, similarly to ABMT, there is little understanding of the underlying basis of the therapeutic effect of mindfulness-based interventions and, to date, no studies have measured the effects of these kind of interventions on food-related AB.

To our knowledge, there have been no RCTs of ABMT in people with obesity or BED. Investigating the clinical potential of ABMT and comparing it with a more established attention training (i.e. a short mindfulness training [MT], for details see below) will shed light on the most appropriate treatment. Furthermore, comparing different types of attention trainings (i.e. MT vs ABMT) in people with obesity will contribute to our understanding of maladaptive cognitive patterns (i.e. AB) related to food craving and overconsumption in this population.

### Aim and objectives

The aim of this trial is to assess the feasibility and acceptability of two different attention trainings (i.e. ABMT and MT) with a waiting-list control group in people who are overweight or obese and to obtain important information for the development a future large-scale RCT.

### Primary objective

To establish the feasibility of conducting a large-scale RCT of attention trainings in patients who are overweight or obese, by assessing recruitment, attendance and retention rates.

### Secondary objectives

To determine the best instruments for measuring outcomes in a future trial by examining the quality, completeness and variability in the data.To estimate the treatment effect sizes and standard deviations for outcome measures to inform the sample size calculation for a large-scale RCT.To determine whether patients who are overweight/obese view computer-based attention trainings as acceptable and credible.To obtain information about patients’ willingness to undergo random allocation to ABMT, MT or waiting list for eight weeks.To evaluate the relationship between AB and eating behaviour.To identify AB modification after training and its association with symptom change.To compare eating behaviour and weight change between conditions before and after training.To identify potential additional underlying mechanisms of attention trainings related to reward processing and self-regulatory processing using neurocognitive tasks.

## Methods

### Design

This feasibility study is a three-parallel group, randomised, waiting-list control trial comparing ABMT versus MT for people who are overweight or obese. The protocol is outlined in Fig. 1 and details of the assessments timepoints are given in Table 1.

**Fig. 1 Fig1:**
[figure not shown]
*Schematic diagram* of study procedures

**Table 1 Tab1:** Assessment timepoints

	Screen visit	Week 1 pre-assessment	Weeks 1–8	Week 8 post-assessment	Week 12 follow-up
Patient information and informed consent	X				
Data sharing Acknowledgement for Headspace® (when applicable)		X			
Eating Disorder Diagnostic Scale (EDDS)	X				
Structured clinical interview for DSM-V (SCID)	X				
Additional eligibility assessment	X				
Visual analogue scale (VAS) for hunger, craving, mood, stress and anxiety levels		X	X	X	
Eating Disorders Examination Questionnaire (EDEQ)		X		X	
Power of Food scale		X		X	X
Mindful Eating Questionnaire (MEQ)		X		X	X
Mindful Awareness and Attention Scale (MAAS)		X		X	
Depression, Anxiety and Stress Scale (DASS-21)		X		X	
State and Trait Anxiety Inventory (STAI)		X		X	
Weight, height and body composition		X		X	
Experimental tasks (Food-Choice task, Bogus taste test, Food-challenge task)		X		X	
Food-ANT		X		X	
Visual Probe Task		X		X	
ABMT/MT			X		
Acceptability questionnaire				X	
Eating habits, self-report body weight					X
Snack Diary (when applicable)			X		
Demographics		X			
Drink and food adherence		X	X	X	

### Setting

The study will be carried out at the Institute of Psychiatry, Psychology and Neuroscience (IoPPN) at King’s College London (KCL) and South London and Maudsley NHS Foundation Trust (SLaM), UK.

### Ethical approval and trial protocol

Ethical approval for the protocol of this study v.2.2 dated 18 October 2018 was obtained from London - City & East Research Ethics Committee (REC ref.: 18/LO/1683). The study is registered on the International Standard Randomised Controlled Trial Number (ISRCTN) registry (registration number: ISRCTN15745838).

### Participants and recruitment

Participants will be recruited via advertisement on the KCL circular mail and social media; posters with general information about the study will be placed on notice boards at various KCL sites and public places. Adverts will also be shown on different online platforms such as the Beat website (the UK’s national Eating Disorders Association), the research team’s departmental website and the MQ mental health charity website. In addition, suitable patients attending the Eating Disorders Unit at SLaM will be invited to take part in the study. Lastly, participants who have taken part in previous research and have consented to be contacted for other studies will be approached.

### Inclusion criteria

Male and female participants will be eligible if they: (1) are aged ≥ 18 years; (2) have a BMI ≥ 25 kg/m^2^; (3) are fluent in English; and (4) give written informed consent.

### Exclusion criteria

Participants will be excluded if they: (1) have a diagnosis of a current other major psychiatric disorder (e.g. major depression, major suicidality, substance dependence, psychosis) needing treatment in its own right; (2) have a past or present DSM-5 diagnosis of anorexia nervosa (AN), bulimia nervosa (BN) or Other Specified Feeding or Eating Disorder (OSFED); (3) have a diagnosis of diabetes mellitus; (4) have recently started psychotropic medication or increased the dose (i.e. within the previous two weeks); (5) take medication for weight loss; (6) are pregnant (either current or in the past six months); (7) have a regular, current or past, mindfulness meditation or yoga practice (defined as > 20 min, twice or more times per week during the past two months); or (8) have visual impairments that cannot be corrected with contact lenses or glasses.

### Sample size

The sample size of this feasibility study is based on standard suggestions considering 12 participants per arm as reasonable sample size for a feasibility trial mainly because estimates of the standard deviation for normally distributed variables tend to stabilise around this size [34]. Considering a sample size of *n* = 36 and assuming the attrition to follow-up rate is a = 0.25, we strive for a sample size of *n* = 45, i.e. 15 participants per group (using an attrition correction factor of 1/(1-a)).

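### The stated attrition correction gives 48 participants (16 per arm), not 45 (15 per arm); at 25% attrition, 45 leaves about 34 completers against a target of 36

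*Protocol article*

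**What the plan says.** The Sample size section gives every element of the calculation.

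- Target: it rests on general guidance, "considering 12 participants per arm as reasonable sample size for a feasibility trial", because standard deviation estimates settle at about that size. For three arms this becomes "Considering a sample size of *n* = 36".
- Attrition: "assuming the attrition to follow-up rate is a = 0.25".
- Result: a total of 45, that is "15 participants per group (using an attrition correction factor of 1/(1-a".

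The Abstract (Design) repeats the total: "Forty-five adults who are either overweight or obese". The Methods (Design) section confirms a "three-parallel group, randomised, waiting-list control trial", so 15 per group and 45 in total agree with each other. No other section gives a different attrition rate or a different inflation formula.

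**The concern.** The target, the attrition rate, the formula and the result are all stated, and they cannot all be true together. The attrition allowance exists to protect 12 evaluable participants per arm, which is the only basis offered for the sample size. If the allowance is too small, that basis fails under the plan's own assumption.

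Two features of the trial make this worth correcting. The secondary objectives include estimating effect sizes and standard deviations to plan a larger trial, and the 12-per-arm guidance is about the stability of standard deviations. Retention is part of the primary objective, so readers will compare observed retention with the planning rate. As written that rate is ambiguous: the text says 25%, while 45 with the stated formula implies 20%.

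**Working it through.** **Inputs**, from the Sample size section: 12 per arm, 3 arms, 36 in total, a = 0.25, inflation factor 1/(1 − a), stated result 45 (15 per arm).

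**Step 1. The stated formula.** 36/(1 − 0.25) = 36/0.75 = 48. Per arm, 12/0.75 = 16. Both are exact whole numbers, so rounding cannot explain the gap of 3 participants.

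**Step 2. What does reproduce 45.**

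- Factor 1 + a with the stated rate: 36 × 1.25 = 45 (12 × 1.25 = 15 per arm).
- Stated factor with a different rate: 36/(1 − 0.20) = 45.

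The first is a common slip, but the article does not show how 45 was obtained, so the error could lie in the formula or in the rate.

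**Step 3. What 45 delivers at 25% attrition.** 45 × 0.75 = 33.75 expected completers, or 15 × 0.75 = 11.25 per arm. The expected shortfall is 36 − 33.75 = 2.25 overall, or 0.75 per arm. The attrition at which 45 leaves exactly 36 is 1 − 36/45 = 20%.

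**Step 4. Chance of reaching the target.** This assumes that participants drop out independently with probability 0.25. That model is an assumption made here and is not in the article.

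| | 45 randomised | 48 randomised |
|---|---|---|
| Expected completers | 33.75 | 36 |
| P(at least 36 completers in total) | 0.280 | 0.577 |
| P(at least 12 completers in a given arm) | 0.461 | 0.630 |
| P(at least 12 completers in all three arms) | 0.461³ = 0.098 | 0.630³ = 0.250 |

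The 48 column is needed to read the 45 column fairly. Inflating for expected dropout sets the target at the mean, so even the correct number often misses it. The error accounts for the difference between the columns, not for the whole of the low figure of about 10%.

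**Step 5. Effect on the stated rationale.** By the normal approximation, the relative standard error of a per-arm standard deviation is 1/√(2(n − 1)).

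- n = 12: 1/√22 = 21.3%.
- n = 11.25: 1/√20.5 = 22.1%.

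For a standard deviation pooled over the three arms, the 95% limits as multiples of the estimate move from 0.81–1.32 (33 degrees of freedom) to 0.80–1.33 (about 31).

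**The case against.** The other side concedes the arithmetic and argues that it hardly matters.

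- **Twelve per arm is a rule of thumb.** The article calls it reasonable, not a minimum, and presents 45 as a number to aim for. There is no power calculation, and the Analyses section disclaims any test of group differences. An expected 11.25 is still close to 12, and step 5 shows that precision barely moves. This stands, and it limits the practical weight of the point.
- **The rate refers to follow-up.** In this protocol, follow-up means the week 12 online questionnaires, whereas the effect size meant to guide the future trial is taken at the week 8 post-treatment assessment. Attrition by week 8 is not given and may be lower; if it were 20% or less, 45 would leave at least 36 at that visit. This also stands, as a qualification: the figure of about 34 completers applies to whichever timepoint the 25% describes. It does not make 45 follow from the stated formula.
- **Retention as an outcome is unaffected.** The 25% is not tied to any progression criterion in the article, so the slip does not bias the retention estimate. This is correct; what remains is the ambiguity about which rate was planned for.
- **The low probabilities alarm more than they should.** This is fair when they are shown alone, which is why the table above pairs them with those for 48.

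None of this reconciles the stated inputs, formula and result.

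**Conclusion.** The concern holds. The stated inputs and formula give 48 (16 per arm), and the article states 45 (15 per arm). At 25% attrition, 45 leaves 33.75 expected completers, 11.25 per arm, against the stated 36 and 12. The figure 45 fits the formula only at 20% attrition.

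The contradiction needs no assumption beyond the article's own numbers. The expected shortfall rests on the 25% rate and applies at the timepoint to which that rate refers; the probabilities also rest on independent dropout. The consequence is small: under one completer per arm and almost no loss of precision for a standard deviation. The sentence should still be corrected, because it is the only justification for the sample size and is wrong as written.

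**What to change.** Correct the sentence in the Sample size section in one of three ways.

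1. Keep 45 and the stated formula, and give the attrition that they allow for: 20%, since 45 × 0.80 = 36.
2. Keep 45 and the 25% rate, and give what is expected to remain: about 34 completers, about 11 per arm.
3. Keep both 25% attrition and 12 per arm, and state 48 (16 per arm), with the Abstract changed to match.

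The first two leave enrolment, the Abstract and the analysis as they are and cost one sentence; the tolerated attrition or the retained sample then reads slightly less favourably. The third adds three participants. Whichever is chosen, the sentence should also say whether the attrition rate refers to week 8 or week 12.

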### Randomisation

Participants will be allocated to either the ABMT, MT or waiting-list condition. Randomisation will be done by minimisation to control for BMI (obese/overweight) and gender (male/female). An independent researcher (not connected with the study) will perform the allocation using a computer programme for the generation of the random component. Allocation for balance between groups will be done manually and will be communicated via email to the researcher for each participant. Participants allocated to the waiting-list condition will be given the option to take the electronic version of the training of their choice (i.e. no randomisation process) once the waiting time is over.

### Intervention conditions

Participants assigned to either of the two intervention conditions will be asked to attend the Institute of Psychiatry, Psychology and Neuroscience eight times during an eight-week period (i.e. once/week). In addition, participants will be instructed to complete an Internet-based version of the allocated training every day for eight weeks at home (except for days when they have their weekly lab-based session).

For every lab-based training session, participants from both conditions will be asked to choose between three high-calorie snacks. The chosen snack will be available to them to activate craving and reward/self-regulation cognitions during training. Visual analogue scales (VAS) for hunger and craving for the chosen snack will be assessed before and after the trainings to measure any potential changes. In addition, to minimise variability in hunger and satiety, participants will be requested not to eat or drink anything (apart from water) 2 h before each training. Before this window, they will be advised to have a light meal. To establish compliance, drink and food adherence for each training session will be recorded.

Adherence to home sessions will be monitored via self-report (i.e. a training log) and through an output generated electronically at the time of each training. Other than these data on compliance, no further data from daily trainings will be collected.

### Attention bias modification training

The aim of the ABMT is to relatively implicitly train participants to ‘look towards’ low-calorie food and ‘look away’ from high-calorie food using a modified version of the anti-saccade task [16], while eye movements will be recorded to assess participants’ training accuracy. For home sessions, participants will be given a tablet (Asus ZenPad 10) with a website version of the ABMT training to use for a daily 10-min session. Participants allocated to this condition will be asked to record their daily accuracy rate on the training.

No side effects or risks of this type of training have been reported. However, because of the intense level of concentration required, participants could report fatigue. To minimise this, participants will be given small breaks (e.g. 2 min) between each block of the training (each training is formed by three blocks). We do not anticipate any other unintended effects of this training.

*ABMT training paradigm overview*: This version of a modified anti-saccade task consists of 360 trials in total. Of these, 180 require participants to look towards low-calorie foods and 180 trials require participants to look away from high-calorie foods. For all trial types, a black fixation point appears for 100 ms, followed by a red or blue fixation point for 500 ms. A blue point indicates that a pro-saccadic eye movement is required (i.e. looking towards the food picture appearing after the fixation point), whereas a red point requires an anti-saccadic eye movement (i.e. to direct the gaze to the opposite side of the screen to where the picture appears). A blank screen gap is inserted for 200 ms between fixation point and picture presentation to speed up subsequent reaction times (e.g. Kissler and Keil [35]) and then a pictorial stimulus (high- or low-caloric food picture) appears on either the left or the right side of the screen for 500 ms. Inter-trial interval is 1300 ms. Trials will be presented in three blocks of each 120 trials.

*ABMT paradigm trial types*: Low-calorie cues are always preceded by a blue dot (indicating that participants should perform a pro-saccade towards the stimulus) and high-calorie food cues are always preceded by a red dot (indicating that participants should perform an anti-saccade away from the stimulus).

*Stimuli:* Participants will view 30 low-calorie food and 30 visually matched high-calorie pictures per block. The position of each picture is counterbalanced for the presentation on the screen side: each picture presented once on the left and right sides of the screen, resulting in the overall 360 training trials (30 food stimuli + 30 non-food stimuli × 2 positions × 3 blocks). The order of trials will be randomised individually.

*Feedback:* Response latencies are recorded during the task to monitor accuracy and provide participants with feedback. For each block, numbers of correct responses are summed up and presented as a percentage score of correct performance to the participant (e.g. 70% correct performance).

